### Recruitment

Every potential study participant, patients, GPs and additionally in the intervention group PTs and home care nurses, will receive written and verbal study information and will be required to give written informed consent. The identification and recruitment of clusters (GP practice and their patients), PTs and home care nurses are presented (see Fig. 1).

**Fig. 1 Fig1:**
[figure not shown]
Recruitment and flow of all participants

In a first step, GP practices will be identified by searching GP registers in each study region. Cooperation networks will be consulted and the project will be presented to professional associations. Included GPs will then select potential patients as participants by searching their data bases for relevant ICD Codes (see Table 1) within the past 3 years. The GP will send a study invitation letter to eligible patients. Interested patients will make an appointment for the informed consent discussion with the GP. If included patients in the intervention group receive home care, their home care nursing services will be informed about the study. The director of the home care service will be asked to select at least two nurses, who are in contact with the participating patient at least than once a week, to attend the educational training (see Implementation strategies). PT practices will be identified through asking included GPs for existing cooperation and through regional searches. Identified PT practices will receive an invitation letter. If interested, the head of the PT practice can select up to two PTs to attend the educational training.

**Table 1 Tab1:** ICD Codes for having recent or chronic complaints of VDB

ICD codes	Explanation
F45.8	Other somatoform disorders
G43.1	Migraine with aura
G62	Other and unspecified polyneuropathies
G63	Polyneuropathy in diseases classified elsewhere
H81	Disorders of vestibular function
I95.1	Orthostatic hypotension
R26 (without R26.1)	Abnormalities of gait and mobility
R29.6	Repeated falls
R42	Dizziness and giddiness

As incentives, participating GP practices receive a case payment per patient (60 €). Participating PT practices will receive a case payment per patient (30 €), and home care services will receive a training on the ‘National Expert Standard in Long Term Care on mobility’ [33] after the study.

### Allocation

GP practices will be randomly allocated to the intervention or control group after written informed consent. Stratified block randomisation by region (two times three clusters in Saxony, two times in south-eastern Bavaria) will be used. The block length will be two, ensuring an equal number of clusters providing the experimental and the control intervention, respectively. The most recent version of the Statistical Analysis System SAS (SAS Institute, Cary, NC, USA) will be used for generating the sequence. Allocation will not and cannot be concealed from the members of the research team distributing the study materials to the care providers. The allocation sequence will be generated by a statistician who is not involved in the study.

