### Sample size

Sample size calculation was informed by data of a cohort study with the same population [32]. Data gave evidence of an ICC = 0.04 and an expected standard deviation of 25. A cluster size of 10 is assumed, i.e. the variance inflation factor is 1 + (10 − 1) × 0.04 = 1.36. The study plans to detect a score difference between intervention groups of at least 12 points [30] on a two-sided alpha level of 0.05 with a power of 80%, resulting in a total sample size of ((1.96 + 0.84)^2^ × 2 × 25^2^ × 1.36)/12^2^ = 92.6. Recruitment of 12 clusters à 10 patients accounts for a dropout rate of 23%. The study will be conducted in two waves, resulting in six clusters (three per study centre) à ten patients being recruited per wave. Current experience shows that a few clusters will possibly fail to recruit the necessary number of patients. In this case, we will recruit more patients in other clusters to compensate for this. To maintain the statistical power of the study, the following rule will be applied: number of patients to be additionally recruited in other clusters = 1.5 × number of patients that some clusters fail to recruit.

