**Delivery**					
Standardised evaluation forms for the educational trainings including supportive materials	X				
Implementation protocol	X				
Field notes via checklist/decision tree				X	
Field notes of contact via telephone or email		X	X	X	
Interviews with all participants				X	X

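### The plan as written does not exclude selection of patients by GPs who have already had arm-specific training, and the shortfall rule adds to this

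*Protocol article*

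**What the plan says.** All references are to the protocol article.

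- **Allocation:** "GP practices will be randomly allocated to the intervention or control group after written informed consent". The section does not say whether this is the GP's consent alone or also the patients'.
- **Recruitment:** consent is required from several groups: "Every potential study participant, patients, GPs and additionally in the intervention group PTs and home care nurses, will receive written and verbal study information". A cluster is described as the practice together with its patients: "The identification and recruitment of clusters (GP practice and their patients), PTs and home care nurses are presented".
- **Recruitment, text at Fig. 1:** the GP carries out each step of patient entry: "Included GPs will then select potential patients as participants by searching their data bases for relevant ICD Codes"; "The GP will send a study invitation letter to eligible patients"; "Interested patients will make an appointment for the informed consent discussion with the GP".
- **Table 3, Delivery:** the row "Standardised evaluation forms for the educational trainings including supportive materials" is marked in the enrolment column, before t0. So is the implementation protocol.
- **Process evaluation:** patient interviews at t0 are planned for about 15 patients from each arm.
- **Control group and Implementation strategies:** control GPs get a 30-minute session on the national guideline. Intervention GPs get a two-hour training that introduces the checklist.
- **Sample size:** if some clusters fall short, "In this case, we will recruit more patients in other clusters to compensate for this", at 1.5 patients for each one missing.
- **Data analysis:** the model contains arm, initial DHI and a random cluster effect. Further fixed effects are ruled out.

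**The concern.** Randomising practices balances practices in expectation. It balances patients only if the way they enter the trial cannot depend on the arm. Where the GP identifies, invites and consents patients after an arm-specific training, that protection is lost. A GP newly trained in vestibular diagnostics and referral to physiotherapy may see different patients as suitable, or persuade them differently, than a GP who has heard a short guideline talk. No intent is needed.

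The difference would then be present at entry and would be read as a treatment effect. More patients would not shrink it. Adjustment for initial DHI removes imbalance in that score, but not in diagnosis, motivation or expected course. The ICD list runs from polyneuropathy and gait abnormality to vestibular disorders, so there is room for the diagnosis mix to differ between arms at the same DHI.

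**Working it through.** **1. What the text fixes about the order**

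| Step | What is stated | What is open |
|---|---|---|
| Allocation | After consent (Allocation) | Whose consent |
| GP training | Training evaluation marked in the enrolment column (Table 3) | Before or after patient invitation within enrolment |
| Patient search, invitation, consent | Done by the GP (Recruitment) | Before or after allocation |
| t0, including initial DHI | Before the intervention (Outcomes) | Before or after allocation and training |

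An evaluation form for a training implies that the training has taken place, and interviews split by arm at t0 imply that the arm is known by about then. Together they make allocation and training before t0 the likelier reading. Neither places training before patient identification or consent, and neither rules it out.

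**2. How many patients the shortfall rule could add**

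Inputs from Sample size: 12 clusters of 10, ICC 0.04, multiplier 1.5. The shortfall patterns are my assumption.

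Added = 1.5 × shortfall. Total = 120 − shortfall + added.

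- 2 clusters short by 5: added 1.5 × 10 = 15; total 120 − 10 + 15 = 125; share 12%.
- 3 clusters short by 5: added 1.5 × 15 = 22.5; total 127.5; share 18%.
- 3 clusters short by 8: added 1.5 × 24 = 36; total 132; share 27%.

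Effective sample size = Σ m / (1 + (m − 1) × 0.04). Planned: 12 × 10 / 1.36 = 88.2. With the additions spread evenly over the other clusters, the three patterns give 89.6, 90.0 and 88.7. For the first: 10 × 11.5/1.42 + 2 × 5/1.16 = 81.0 + 8.6 = 89.6. So the rule preserves precision as intended. It does nothing for comparability.

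**3. Illustration of size**

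The documents give no figure for selection. Assume that 10–20% of intervention patients are chosen because they look likely to respond, and that these improve by 10 points more than an unselected patient. Bias = 0.10 to 0.20 × 10 = 1 to 2 DHI points; 1/12 to 2/12 = 8–17% of the target difference.

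For scale against sampling error, the plan's own expression comes first: (1.96 + 0.84)² × 2 × 25² × 1.36 / 12² = 92.56, which matches the printed 92.6. (This is the usual formula for one arm, although the text calls the result a total. That is a separate matter and is used here only for scale.)

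With N patients in all, SE = 25 × √(2 / (N / 2 / 1.36)): 6.06 for N = 92.6 and 5.32 for N = 120. With no true effect and a bias b left after adjustment, two-sided type I error = 1 − Φ(1.96 − b/SE) + Φ(−1.96 − b/SE):

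| b (DHI points) | N = 92.6 | N = 120 |
|---|---|---|
| 0 | 5.0% | 5.0% |
| 2 | 6.3% | 6.6% |
| 4 | 10.1% | 11.7% |

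These use the normal approximation and the plan's SD of 25 without any gain from baseline adjustment.

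**The case against.** A reader might infer that practices are definitely randomised and trained first, and that patients are recruited and baselined only afterwards. The article does not support that as fact. Patients must also consent and a cluster includes its patients, so allocation after patient consent fits the Allocation sentence. The recruitment text runs through search, invitation and consent before it mentions the intervention group. Fig. 1 and Table 2 may settle the order. Table 3 has one undivided enrolment column and cannot order events within it. Its training row is not limited to GPs, and at least the home care nurses are picked for training only once a patient of the intervention group is included. All of this stands, and it is why the point is confined to what the plan fails to exclude.

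Other parts stand only in part:

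- **Limited GP discretion.** The ICD list, the three-year window and the DHI threshold of 12 bound the pool. They do not determine who is invited or persuaded.
- **Masking.** The plan aims to mask GPs and patients, and a GP may not know what the other arm receives. But masking is only an aim, given as a guard against performance bias, and hiding the label does not undo what a training teaches about suitable patients. Blinded assessors protect measurement, not entry.
- **Shortfall rule.** With two waves, a first-wave shortfall could be met in practices not yet allocated. The rule does not require this, and a second-wave shortfall could not be handled that way unless some second-wave practices were still unallocated.
- **Small size.** The illustrated 1–2 points lie well below one standard error and rest on invented inputs. This limits the weight of the point, but the protection is cheap.

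**Conclusion.** The concern holds in a limited form. The article leaves the order of allocation, training, patient consent and t0 open, and the likelier reading puts allocation and arm-specific training before t0. Since the GP controls patient entry, selection by an already trained GP is not excluded. The shortfall rule adds to this because it has no limit on allocation status, arm or source list, and adjusting for initial DHI alone would not repair the result.

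That such selection will happen, or that the initial DHI is measured after allocation, cannot be concluded from the text. The size of any bias is unknown. The 1–2 DHI points and the 12–27% share of added patients rest on assumed inputs. If Fig. 1 shows patient consent and baseline before allocation, one clarifying sentence settles the main point, and only the shortfall rule still needs limits. This should be changed, but it does not by itself invalidate the trial.

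**What to change.** 1. **State the order** in the Allocation section, including whose consent precedes randomisation.
2. **Practices not yet allocated:** complete GP consent, ICD search, a frozen list of eligible patients, invitation, patient consent and t0 (with the DHI criterion). Only then release the allocation and give the training.
3. **Shortfall patients:** draw them only from the list frozen before allocation, invited in random order and by the same rule in both arms.
4. **Practices already allocated:** record the dates of allocation, training, patient consent and t0. Flag every patient enrolled after allocation and pre-specify a sensitivity analysis without them. If the dates show that this applies to nearly all patients, that analysis will carry little information and the reporting in item 5 matters most.
5. **Reporting:** give the numbers listed, invited and consented by arm.

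Cost: existing steps are re-ordered, with no extra visits. Training comes later, and a gap may open between t0 and the start of the intervention. Because outcomes are timed at 4 and 6 months, that gap should be kept short and similar in both arms. By Trial status, the first cluster entered in December 2021 and the last was due in January 2023, so item 2 comes too late for most practices. Items 1, 4 and 5 remain feasible at little cost, and item 3 applies wherever top-up recruitment is still open and a pre-allocation list exists.

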### Intervention

#### Experimental intervention

The intervention is an algorithmized evidence-based multidisciplinary CPW to enhance the care of older persons with VDB and thus promote their mobility and participation in daily living. It illustrates all steps of the patient pathway through a standardised approach consisting of two main components:A paper-based *checklist for standardise clinical decision making*, which contains evidence-based diagnostics, treatment and referral options for the whole treatment period and is applied by previously trained GP. The aim of the checklist is to help the GP to make a classifying diagnosis, to guide the next steps and to prioritise them.A *decision tree* for evidence-based physiotherapeutic clinical reasoning and treatment of VDB. It consists of recommendations and options for anamnesis (including information about clinical pattern), specific assessments, treatment and evaluation. The decision tree will be applied by previously trained PT, if the treating GP prescribes physiotherapy.

At the beginning of the 4-month intervention period, the patients make an appointment with their GP who performs the anamnesis and the examinations based on the checklist. The anamnesis involves questions regarding the quality, character, frequency and duration of VDB and accompanying symptoms. Then, further examinations like position manoeuvre and neurological tests will be undertaken by the GP. Depending on the results of the anamnesis and examinations, the checklist contains suggestions for further referral and treatment (see Fig. 2). Referral suggestions can be the referral to a neurologist, otorhinolaryngologist, internist/cardiologist and PT. Treatment options may include symptomatic bridging therapy with medication or general treatments such as medication adjustment. The treatment by and therefore the referral to a trained PT is recommended when the checklist/GP comes to the following conclusions: the patient suffers from benign paroxysmal positional vertigo, other factors requiring examination by another physician specialist can be excluded and/or has taken place before with no results.

**Fig. 2 Fig2:**
[figure not shown]
Intervention flow

The trained PT will use the decision tree for clinical reasoning and planning and applying the treatment. According to the decision tree, the PT will use systematic recommendations and options for a physiotherapeutic anamnesis, which leads to specific hypotheses. Following the algorithm, the PT is then able to differentiate and choose the right physiotherapeutic assessment. Based on the results, the decision tree leads him/her to a specific hypothesis and corresponding evidence-based treatment options (the main focus is on vestibular rehabilitation) including educational material for the patient, like home exercise programs and flyers with information. Last step will include the evaluation and documentation of the chosen therapy.

At the follow-up-visits after 4 weeks and 3 months, the GP will use the checklist again. In case of worsening of symptoms or 8 weeks PT without improvement, a referral to a medical specialist is recommended. In the event of a slight improvement in symptoms, PT is recommended for a further 4 weeks. If there is significant improvement after 4 weeks, only the second follow-up examination is suggested. In the event of significant improvement after 3 months, the treatment is successfully completed within the context of the study. A modification of the intervention is not planned. There are no restrictions regarding concomitant treatments and interventions during the trial.

#### Control group

To avoid performance bias, we aim to keep GPs and patients masked regarding group allocation. Therefore, we provide an active control intervention for the control group cluster (GPs and their patients). It consists of a 30-min online educational training on the German national guideline ‘acute dizziness’ for GPs [17], which is held by a GP.

#### Logic model

The logic model (see Additional file 1) illustrates the relationship between the planned work (‘resources’ and ‘activities’) to implement the intervention (implementation strategies), the expected mechanism of impact (based on a behaviour change theory), the intended results (realised intervention with ‘output’, ‘outcome’ and ‘impact’) and categories of possible influencing factors. The structure of the logic model follows the Logic Model Development Guide [34]. As behaviour change theory, we applied the capability, opportunity and motivation behaviour (COM-B) model originating from the behaviour change wheel [35] as theoretical foundation for a structured development of implementation strategies and there with to support the intended behaviour change for both, the health professionals and the patient. The basic assumption is that a behavioural change of health professionals is a prerequisite for a change in patients’ health behaviour. The use of resources and the improvement of these through certain activities (e.g. knowledge enhancement through training) influence the capability, motivation and opportunities, which ultimately alter the behaviour of the health professionals. This can lead to a behaviour change at the patient level, e.g. by passing on the gained knowledge to patients, thus influencing their COM-B. As a result, behaviour change can contribute to an improvement in mobility and participation of older patients with VDB. For classifying and identifying influential factors on implementation, the five main elements of Consolidated Framework of Implementation Research are used [36].

### Implementation strategies

To reach the study target, various implementation strategies will be delivered (see Table 2). Some of these strategies have been tested in the pilot study and according adaptations were made [25].

**Table 2 Tab2:**
[figure not shown]

[figure not shown]
Schedule of enrolment, interventions, research outcomes and assessments according to SPIRIT

*GP* general practitioner, *PT* physiotherapy, *VDB* vertigo, dizziness and balance disorders

In the intervention group, GPs and if requested their medical assistants will participate in a two hours lasting educational training. The training will be held by a VDB expert and neuro-otologist and will include an update on recent diagnostic and therapeutic developments for VDB in older patients, as well as an introduction into the use of the checklist for diagnostic screening. The PTs will receive a 1-day educational training called ‘Dizziness and/or balance disorders in the vestibular rehabilitation of older patients in primary care’ which enables the participating PTs to understand the procedure according to the decision tree and enables them to apply it. To make sure, that the PTs can transfer their knowledge into practice, there will be the opportunity so share treatment videos and receive feedback from the expert. Both events will be held live online. After 8 weeks, GP practices and PTs will be invited to a 1-h online moderated follow-up workshop to exchange experiences about the study and ideas to improve the communication in an interdisciplinary team working in primary care. A pocket card for the home care nurses serves as a reminder on their role as supporters of the patients’ adherence to the intervention (reminders on potential physiotherapeutic exercises, making and keeping appointments, filling out the exercise diary, fall prevention measures). In addition, they will receive a training about VDB in older people, fall prevention and their role in the study. All participants will receive step-by-step instructions on the study process. Moreover, there will be a telephone hotline for all participant groups to answer their questions on content and methodology and to respond to problems or needs in a timely manner.

### Outcomes

The primary and secondary outcome will be assessed on patient level in the intervention group and control group at three measurement points: at baseline before the intervention (*t*_0_), after 4 months (*t*_1_) and after 6 months (*t*_2_). Additional data on GP practices, PT practices and home care nursing services level will be assessed at *t*_0._ For an overview of the research outcomes and assessments, see Table 2.

#### Primary outcome measures

##### Dizziness handicap inventory

The impact of VDB on participation and mobility of patients will be assessed using the Dizziness Handicap Inventory (DHI). It is a condition-specific instrument to assess self-perceived disability, such as limitations in mobility and activity and participation in older patients [37]. The DHI contains 25 items of three different subscales: Functional subscales (nine questions), emotional subscales (nine questions) and physical subscales (seven questions). The patients will rate their problems on a scale ranging from ‘no’ (0 points) and ‘sometimes (2 points) to “yes’ (4 points). The total score ranges from 0 points to 100 points, while the higher the score, the greater the self-perceived handicap. A mean decrease of 12 points between *t*_0_ and *t*_2_ is considered as a clinically meaningful difference [30]. For our study, we will use the Dizziness Handicap Inventory—German Version (DHI-G). It has high reproducibility and good internal consistency [29, 37].

#### Secondary outcome measures

##### Physical activity

The main secondary outcome is the qualitative and quantitative change in daily-life physical activity measured by wearable sensor-based actigraphs from movisens [38]. In addition, patients will be asked to fill in a physical activity diary about their activities of daily living and occurrence of VDB.

